## Trends in prevalence of Neonatal deaths

Worldwide, 2.4 million newborns died in the first 28 days of life in 2019. There are approximately 7 000 newborn deaths every day, especially in sub-Saharan Africa and South Asia[[81](#_ENREF_81)]. A systematic review conducted in Kenya and South Africa showed that in 2018, the Neonatal Mortality Rate (NMR) for Kenya was 19.6 deaths per 1000 live births and the NMR of South Africa was 10.7 deaths per 1000 live births[[82](#_ENREF_82)]. About 50% and 75% of neonatal mortalities occur in the first 24 hours after birth and within the first week of life of the newborn, respectively[[31](#_ENREF_31)]. In Ethiopia, about 87,000 neonates die annually, of which 85% of births are at home [[50](#_ENREF_50)]. A recent prospective cohort study conducted in Aroresa district in Sidama region showed that the neonatal death was 41 per 1000 live births in the study period[[83](#_ENREF_83)]. The majority are preventable through simple, low-cost interventions and one-half or more of these deaths occur in the home [[84](#_ENREF_84)]

## Causes and Timing of Neonatal Death

The main causes of death are asphyxia, hypothermia, hypoglycemia, infection, and complications related to prematurity[[31](#_ENREF_31), [32](#_ENREF_32)]. A prospective cohort study conducted in 2017 among neonates in Northern Ethiopia in showed that two thirds of deaths were attributable to prematurity 23 (34%) or asphyxia 21 (31%). The other study showed that prematurity takes the part in the early neonatal period (37%) , while asphyxia (35%) was more common in the late neonatal period [[33](#_ENREF_33)]. Another study showed the association that, preterm babies were 2.2 times higher risk than term developing birth asphyxia [AOR = 2.20; 95% CI (1.02, 4.76)]. Similarly, the weight of the neonate had also a significant association with birth asphyxia[[34](#_ENREF_34)]. A study conducted in eastern Uganda showed that major (50%) contributing delays to newborn death were caretaker delay in problem recognition or in deciding to seek care were 50%[[32](#_ENREF_32)].

So far, different studies have been shown the gap of health workers who are working at health centers, hospitals and health posts towards neonatal health care. Interventions also implemented on health workers at health centers and hospital level. However, there is limited evidence of actions to improve the quality of services and capacity of health extension workers. Therefore, the main purpose of this study is to improve the quality of community based maternal and neonatal health care through enhancement improving of health extension workers performance at Sidama Regional state.

**Outcome variable**

Reproductive health history factors

Parity, Gravidity , complication

Gestational age at first ANC, Receiving ANC 4+ number of children,

Reproductive health utilization related factors

Distance from health, Age at first birth, distance from the health facility, women autonomy, and mass media exposure, lack of information, inadequate and poor quality services, cultural beliefs,

**Socio demographic economic factor**

Age, religion, marital status, educational status of woman and spouse, occupation, Wealth index, residence

**Intervention**

Community support groups participatory learning action monthly meeting, Facilitation training for HEWs and for supporting health facility staff

ANC4+ utilization

Continuum of care

**Exposure variable**

Barrier and challenge of implementation of the intervention

Figure. Conceptual framework for continuum of care for maternal health adopted from different literature.

Output /Out come

**Process**

**Input**

Community based neonatal Health Care Intervention Packages

Postnatal Care

- Immediate and thorough drying
- Initiation of breathing
- Immediate skin-to-skin contact
- Delayed cord clamping
- Initiation of breastfeeding in the first hour
- Thermal care practice
- Identification, management & referral for neonatal Complications/danger signs

Improved neonatal health care practice (including the thermal care

**1.** Provision of training for health extension workers and health development team leaders

**2**. Participatory learning and action meeting with community health actors (CHWs, CHDTLs, Edir, religious, youth, kebele leaders, male agricultural dev. Leaders, and influential elderly peoples)

3. Regularmeetingfor discussion with HEWs+ HDTLs + community leaders (every month)

Increased rate of early initiated and exclusive BF

Improved early detection &Mgt of neonatal illnesses

3. Collaborative meeting

Improved referral system

Identification & referral with neonatal complications/danger signs

Fig.1. Conceptual framework of model for community based neonatal health care intervention adapted from International Initiative for Impact Evaluation & reading different literatures. Source: International initiative for impact evaluation: A systematic review 005

**Overall aim:**

The aim of the proposed trial is to evaluate the collective effectiveness of a package of community-based interventions on improving continuum of maternal and newborn healthcare.

**Objectives:**

1. To evaluate whether a set of community-based intervention improve completion of maternal continuum of care : A) The overall completion rate with composite result of combination of at least four antenatal care contacts, delivery in a health facility with skilled provider, and at least four postnatal care contacts and completion rates of each three components of the continuum of maternal care. B) Explore the experience of mothers and care providers on the effect of the intervention for maternal care, including the challenges and opportunities.
2. To determine the effectiveness of the community-based strategies on improving utilization of essential and emergency newborn care: A) WHO recommended four elements of essential newborn (immediate and thorough baby drying, skin-to-skin contact, initiation of early breast feeding within first hour, and delayed cord clamping). B) identification and referral of severely sick babies such as babies with danger signs. C) Cost-effectiveness of the intervention on improving maternal and newborn continuum of health care.

# Research question

1. What is the base line information of maternal continuum of care before the SeMaNiH trial intervention among intervention and control groups?
2. What will be the effect of SeMaNiH trial on ANC utilization among the intervention and control groups?
3. What is the effect of SeMaNiH trial intervention on the maternal continuum of care among intervention and control groups?
4. What are the barriers and challenges of the implementation of SeMaNiH trial intervention in the community?

# General objective for PhD candidate one

The general objective of this cluster randomized trial is to implement and assess the effect of package of community-based interventions on improving maternal health services between September 2023 and September 2024 in Sidama Region State, Ethiopia,

**Specific objectives**

1. To describe the pre-trial baseline status of drop out in the maternal continuum of care in terms of antenatal care utilization (ANC4+), Institutional delivery, postnatal care within 48 hrs. (Paper I)
2. To identify community based maternal health care practice received from community health workers among pregnant mothers in sidama regional state from March 2022 to March 2023 (Paper II)
3. To evaluate the effectiveness of package of community-based interventions on improving the proportion of institutional delivery and postnatal care with skilled health professionals( paper III)
4. To explore the challenges and opportunities related to capacitating the community health actors to improve maternal continuum of care (IV)

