## Statement of the problem

Every year, more than 60 million women give birth at home without the benefit of skilled care. Each year, half million women die as a result of pregnancy and childbirth complications. The majority of these mortalities occur in sub-Saharan Africa and South Asia [[19](#_ENREF_19)].

Ethiopia have reduced maternal mortality rate from 720 in 2000 to 412/100,000 live birth in 2020. These are great achievement , but still too high[[20](#_ENREF_20)]. The global agenda is through sustainable development goals (SDGs) is to reduce maternal mortality ratio to less than 70 per 100,000 live births and this requires substantially improved maternal health service [[21](#_ENREF_21)].

Maternal causes of death are classified in to direct and indirect cause of death. Three fourth of maternal death are due to the direct cause of maternal mortality among this. Keeping the regional variation in place globally among the direct cause of maternal death hemorrhage , pregnancy induced hypertensions and sepsis were the leading cause [[22](#_ENREF_22)]. In Ethiopia three major direct causes resulted in three fourth of maternal death, these are hemorrhage, hypertensive disorders, puerperal sepsis[[23](#_ENREF_23)]. Receiving all package of skilled care during antenatal care (ANC), delivery and postnatal period by all women and children at the appropriate level and time reduce mortality and improved health status. Women in rural area deprived of access; as a result there is disparity in utilization of maternal services between urban and rural[[24](#_ENREF_24), [25](#_ENREF_25)]. Furthermore, low level of taking the recommended ANC on time and low completion of the continuum of care (ANC4+, SBA, and PNC within 2 days after birth) by rural women was very indicating inaccessibility for skilled attendant[[26](#_ENREF_26), [27](#_ENREF_27)].

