**Outcome and process indicators**

The primary maternal outcome measure is the completion rate of essential maternal care. We define a continuum of care completion as follows:

1. fully completed care when a mother has received four or more antenatal care, delivered in a health facility with a skilled attendant, and received at least four postnatal care (first 24 hours, 48-72 hours, 7-14 days, and six weeks after delivery) from HEWs or other health professionals within the first month after delivery. Because maternal completion of these essential care components will have an implication for newborn health and survival, and essential newborn care is given simultaneously during delivery and postnatal care, the completion of essential newborn care will be analyzed in relation to the maternal completion rate.
2. Emergency home-based care when the delivery occurred at home and mother and baby received immediate visit at home by HEWs or a higher health professional.
3. Sub-analysis on the primary outcome will compare intervention with control clusters separately on antenatal care completion rate, rate of facility delivery, proportion of assistance received immediately form HEWs or other professionals when a birth occurred at home, and proportion of mothers who stayed at maternal waiting shelters immediate days before delivery.
4. Proportion received financial, transport, and family care support from community resource persons (COLs) when a support is critically needed.
5. The proportion of newborn babies received the four essential newborn care services (immediate and thorough drying, skin-to-skin contact, immediate breastfeeding initiation, and delayed cord clamping)
6. Emergency newborn sickness identification and referral rates.
7. Secondary outcome measure will be on whether the intervention affected reduction of neonatal mortality and stillbirth rates.

For newborn babies, we will measure and compare with the control arm the proportion of babies immediately put to breastfeeding and exclusively feeding until at least a month after birth, the proportion of babies received essential thermal care (wrapping in close, skin-to-skin contact to mother immediately, delayed baby bathing), baby resuscitation at home and in clinics, and proportion of babies received emergency treatment and referrals when they had danger signs.

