**Data collection**

Data will be collected by trained independent data collectors a maximum of five times at households and from health facility records.

First, we will collect data when the mother’s gestation is 20th to 26th week when she formally recruited for subsequent follow-up. This period matches with the time when a mother became pregnant after the start of the intervention process in the intervention cluster. In other words, the mothers who enter the first data collection and follow-up phase on their 20th to 26th week of gestation has been exposed to interventions since they were pregnant. In this first round of data collection, data will be collected on basic socio-demographic and important variables for important covariates such as wealth status indicators, distance to health facility, history of healthcare utilization during the previous pregnancy and delivery.

Follow-up data collection will include the second to the fifth rounds of data collection. The second round will be 10 weeks after the first data collection (30^th^ to 36^th^ week of gestation). This data collection will mainly focus on information about variables related to the continuation of antenatal care utilization and whether the mother had pregnancy related complications and severe sickness, including information on received healthcare for sickness.

The third round of data collection is on the fourth day after delivery. The main variables in this round of data collection include variables on antenatal care completion, delivery information such as place of delivery, delivery attendant, utilization of postnatal care during the WHO recommended first 24 hours and 48-72 hours after birth, whether the mother received any financial, transport, or family care support from the COLs support system to reach to health facility, whether the mother stayed in the maternal waiting shelter nearby health facilities the immediate days before delivery, delivery outcome (livebirth or stillbirth). Additional information will include about maternal and newborn complications during delivery, essential newborn care provided during delivery (resuscitation, umbilical care, thermal care, initiation of breastfeeding, treatment for severely sick and premature babies).

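### The baseline paper measures the maternal continuum with postnatal care within 48 hours and the trial with four postnatal contacts, so baseline completion is not directly comparable with the primary outcome

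*Protocol*

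**What the plan says.** **Baseline.** Under the specific objectives for PhD candidate one, Paper I is to describe drop-out before the trial in terms of "antenatal care utilization (ANC4+), Institutional delivery, postnatal care within 48 hrs". The Statement of the problem uses a very similar construct: "low completion of the continuum of care (ANC4+, SBA, and PNC within 2 days after birth".

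**Trial outcome.** Objective 1A builds overall completion from "at least four antenatal care contacts, delivery in a health facility with skilled provider, and at least four postnatal care contacts". The section on outcome and process indicators adds timing: the mother has "received at least four postnatal care (first 24 hours, 48-72 hours, 7-14 days, and six weeks after delivery". The same sentence ends with "from HEWs or other health professionals within the first month after delivery".

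**One name for both.** Research question 1 asks "What is the base line information of maternal continuum of care before the SeMaNiH trial intervention among intervention and control groups". Research question 3 asks for the effect of the intervention on that same continuum in the same groups.

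**Follow-up items.** The third data collection round, on the fourth day after delivery, lists "utilization of postnatal care during the WHO recommended first 24 hours and 48-72 hours after birth". Later rounds cover the 7-14 day and six-week contacts.

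**Analysis.** The analysis plan is an intention-to-treat comparison of arms that allows for clustering. It states no before-after contrast and no adjustment for baseline completion.

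**The concern.** The protocol uses one term for two indicators. A reader who takes the research questions at face value will expect Paper I to give the starting level of what the trial later tries to raise, and to show whether the arms started level on it. As defined, Paper I does neither for the four-contact composite, because nothing in its stated definition reaches the later postnatal contacts.

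This matters more than usual for two reasons. There are only 10 clusters per arm, and allocation was stratified on population size and distance but not on prior completion, so a chance difference in prior completion is plausible. The postnatal component is also the one that the Introduction singles out as decisive for improving the continuum.

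**Working it through.** **1. The plan's own figure.** Inputs from the sample size section: control 0.20, intervention 0.30, z-values 1.96 and 0.84, cluster size 150, ICC 0.01.

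- Individual randomisation: (1.96 + 0.84)² × (0.20 × 0.80 + 0.30 × 0.70) / 0.10² = 7.84 × 0.37 / 0.01 = 290.08 per arm.
- Design effect: 1 + 149 × 0.01 = 2.49.
- Product: 290.08 × 2.49 = 722.3, rounded up to 723 as stated.

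The baseline definition does not enter this calculation, so aligning the definitions changes no stated number.

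**2. The two definitions side by side.**

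| Component | Baseline (Paper I) | Trial composite |
| --- | --- | --- |
| Antenatal | four or more | four or more |
| Delivery | institutional | facility, with a skilled provider |
| Postnatal, 0-24 h | counts | required contact |
| Postnatal, 24-48 h | counts | in no listed window |
| Postnatal, 48-72 h | does not count (beyond 48 h) | required contact |
| Postnatal, 7-14 days | does not count | required contact |
| Postnatal, six weeks | does not count | required contact |

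The first row matches and the second nearly does. The postnatal rows overlap only in the first 24 hours and at the 48-hour boundary.

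**3. Bridging from follow-up.** A mother whose only early contact is at 30 hours counts at baseline. At follow-up she falls after the first listed window and before the second. Unless the form records contact times, the 48-hour measure cannot be rebuilt exactly from the listed round-three items.

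**4. Direction.** If the four timed windows are required, any woman who meets the trial's postnatal component had a contact in the first 24 hours, and so also meets the 48-hour component. The trial's delivery component is the same or stricter. In the same women, the four-contact rate therefore cannot exceed the 48-hour rate. If any four contacts suffice, as Objective 1A can be read, this ordering is not guaranteed.

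**5. Size.** The documents give no four-contact rate and no local 48-hour rate. As pure assumption: with 20% on the 48-hour measure, and a quarter to a half of those women also having all four contacts, the four-contact rate would be 0.20 × 0.25 = 5% to 0.20 × 0.50 = 10%. Neither input has a source in the protocol for these clusters.

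**6. Why a local four-contact level would be informative.** The 20% planning rate matches the Introduction's published Ethiopian figure, whose postpartum element is not stated as four contacts. With 1000 per arm, 100 per cluster and ICC 0.01, the design effect is 1 + 99 × 0.01 = 1.99 and the effective size is 1000 / 1.99 = 502.5 per arm. Normal-approximation power, without a small-cluster correction, for assumed control rates:

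| Control rate | Planned ratio (0.30 / 0.20 = 1.5) | Planned +10 points |
| --- | --- | --- |
| 5% | 37% | above 99% |
| 10% | 67% | 99% |
| 15% | 86% | 98% |
| 20% | 96% | 96% |

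Example for 10% against 15%: the standard error is √(2 × 0.125 × 0.875 / 502.5) = 0.02086 under the null and √((0.09 + 0.1275) / 502.5) = 0.02081 under the alternative. Then (0.05 − 1.96 × 0.02086) / 0.02081 = 0.44, which gives 67%. Whether a lower control rate would hurt depends on which effect scale is realistic.

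**The case against.** A reader might infer that the baseline cannot describe, compare or adjust for anything relevant to the trial. The documents do not support that.

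- The antenatal and delivery components are broadly common, and the outcome section compares the arms "separately on antenatal care completion rate, rate of facility delivery". The baseline can serve those parts directly.
- A covariate need not be identical to the outcome. A related cluster-level rate can still be useful for adjustment.
- The baseline survey is not the only check on imbalance. Recruitment data include wealth, distance and use of care in the previous pregnancy, and Table 1 compares the arms on population, staffing and distance.

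A reader might also infer that the trial result will show a false rise or fall. That needs a before-after comparison, and the analysis plan states none. The choice of baseline covariates is commonly left to the statistical analysis plan, so its absence here is not a defect.

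Two further points have weight. Paper I's text states the aim of one paper; it does not show that the survey left later contacts unrecorded, and the listed round-three items are not the questionnaire. The same candidate's Paper III is framed around institutional delivery and skilled postnatal care, which is closer to Paper I's items than the four-contact composite is.

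These arguments limit the point without removing it. Research questions 1 and 3 still apply one name to indicators that differ in the postnatal component, and no text says how they will be linked.

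**Conclusion.** The mismatch is real and confined to the postnatal component. Baseline completion as defined is not directly comparable with the primary outcome, and supplies neither a baseline level nor a balance check for it. It remains informative on antenatal care and facility delivery. The randomised post-intervention comparison and the 723 per arm stand.

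No size can be attached from the documents. The 5-10% and the power figures rest on assumed rates and should be used only as such. The conclusion assumes that Paper I will use the stated definition and no other; if the survey recorded later contacts, the gap closes with one tabulation. This is an inexpensive improvement, not a threat to validity.

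The target definition is itself unsettled: a six-week contact cannot also fall within the first month after delivery. Those two limits must be reconciled before any baseline can be aligned with the composite.

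**What to change.** 1. Reconcile the six-week contact with the first-month limit in the outcome section, so that the composite has one definition, and use it in the objectives and research questions.
2. If the baseline survey recorded later postnatal contacts, tabulate the four-contact composite by cluster and arm alongside the 48-hour measure.
3. If it did not, label the baseline as a different indicator. Record the time of each early postnatal contact at the day-4 round, so that contacts at 24-48 hours are captured. Report the 48-hour composite by arm at the end of the trial as a secondary bridging measure.
4. In either case, use the cluster-level baseline completion value to describe balance, and prespecify it as a covariate in the primary analysis.

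Cost: at most one questionnaire field, one extra table and one model term, with no new visits or participants. In a cluster-level analysis the covariate takes one degree of freedom, from 20 − 2 = 18 to 17 before any terms for strata. In return the trial gains a like-for-like baseline and possibly some precision.

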**PhD candidate 2 : Newborn (neonatal) Health**

# General Objective:

To determine whether a community-based capacity-building intervention aimed to improve the continuum of maternal and newborn care in Sidama regional state improves neonatal health care services utilization.

